### Economic evaluation

The economic evaluation will adopt the viewpoint of the German health and nursing care insurance, adding up all costs and savings relevant from the viewpoint of health care insurers and party payers. Assessment will include costs for optimisation of usual care for both groups, costs for using the fall risk assessment tool in the IG as well as medical and nursing care costs following falls for both groups. Costs for the interventions will be estimated based on information from trial records. The analysis will adopt an incremental approach such that data collection will concentrate on resource use differences between study groups. The process of collecting data on resource use will be undertaken separately from data collection on unit costs. Resource use data due to fall related health care will be collected by the investigators during the personal visits using a cost component protocol. The documentation sheet has been successfully evaluated in a recent economic evaluation of a randomised controlled trial [19]. Unit costs will be collected from different sources including published data, health insurances, and various health care providers.

At present, it is not possible to state with certainty which form of economic analysis will be employed, since this will be driven in part by the clinical study results. If a difference in the primary endpoint is observed, then a cost efficacy analysis will be conducted. Otherwise a cost comparison analysis will be conducted. Since cost data will be available for the duration of the trial only, the appropriate effectiveness measure is the one that allows treatment effects during the trial only. A sensitivity analysis on the key variables that might influence the result of the economic evaluation will be carried out.

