### Sample size calculation

It is assumed that about 45% of the participants in the control group will experience at least one fall in 12 months with an intra-class correlation coefficient of ICCC = 0.075. A cluster-randomisation with about 20 participants in each cluster leads to a variation inflation factor of VIF = 2.425. Assuming that 20% of the participants will not complete follow-up and furthermore assuming an absolute difference of 15% (incidence of fallers in the Downton Index-group: 30%) to reach a significant result to the level of alpha = 0.05 with a power of 80% a total sample size of n = 1,080 participants is needed. Therefore the sample size comprises a total of 54 clusters with about 20 participants each.

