### Statistical analysis

The main outcome is the proportion of persons with at least one fall and will be analysed by using a chi-square test adjusted for cluster randomisation [17]. The effect of the risk assessment tool will be expressed as relative risk, difference in absolute risk, and number needed to treat. For risk differences 95% confidence intervals will be calculated using a method appropriate for cluster-randomised trials [18]. For all other follow up data the cluster will be used as unit of analysis. For statistical comparisons between the groups the Wilcoxon rank sum test will be performed. Two-sided p ≤ 0.05 will be regarded as significant. Interrater reliability will be calculated using kappa statistics.

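### The economic evaluation drops to a costs-only comparison unless a difference in fallers is observed, a trigger that is undefined and that a non-significant result cannot justify

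*Protocol article*

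**What the plan says.** The Economic evaluation section of the protocol article leaves the form of the analysis open, to depend partly on what the trial finds: "it is not possible to state with certainty which form of economic analysis will be employed, since this will be driven in part by the" (the sentence goes on to name the trial's findings). It then gives the rule: "If a difference in the primary endpoint is observed, then a cost efficacy analysis will be conducted. Otherwise a cost comparison analysis will be conducted". A sensitivity analysis on key variables is promised under either form.

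The section does not define an observed difference. The nearest criterion is in the Statistical analysis section: "Two-sided p ≤ 0.05 will be regarded as significant". That section also plans a relative risk, a risk difference with a cluster-appropriate 95% confidence interval, and a number needed to treat. None of these is tied to the choice of economic analysis.

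The Sample size calculation section sizes the trial for superiority only, at 45% against 30% fallers. The article gives no equivalence or non-inferiority margin.

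**The concern.** Comparing costs alone answers the payer's question only when effects can be taken as equal. A superiority test that fails to reach significance does not establish that. It is an expected result when the true effect is smaller than the one the trial was sized for, whether the tool helps or harms.

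The trigger also fails if read literally. Two observed proportions are almost never identical, so some difference will nearly always be observed and the second branch would hardly ever apply. The rule is therefore either close to inoperative or, on the significance reading, unsound.

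At stake is whether the trial reports what the tool costs in relation to the falls it prevents or causes. In the second branch that relation is not estimated, although both costs and falls are collected. The Study design and setting section announces a full economic evaluation, and a comparison of costs alone does not relate costs to effects.

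**Working it through.** **Inputs from the Sample size calculation section.**
- Control risk: "about 45% of the participants in the control group will experience at least one fall in 12 months".
- Clustering: "intra-class correlation coefficient of ICCC = 0.075".
- Inflation: "about 20 participants in each cluster leads to a variation inflation factor of VIF = 2.425".
- Also 30% fallers under the Downton Index, 20% loss to follow-up, two-sided alpha 0.05, power 80%, 54 clusters and 1,080 residents.
- Assumption: 1:1 allocation. The article does not state a ratio; it gives permuted blocks to avoid unequal sample sizes.

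**Step 1: reproduce the plan's own figure.** VIF = 1 + 19 × 0.075 = 2.425. The two-proportion formula with pooled null variance gives

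n = [1.96·√(2 × 0.375 × 0.625) + 0.8416·√(0.45 × 0.55 + 0.30 × 0.70)]² / 0.15² = 162.3.

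The continuity correction, (n/4)·[1 + √(1 + 4/(n × 0.15))]², raises this to 175.4, so 176 per arm. Then 2 × 176 × 2.425 / 0.80 = 1,067, or 53.35 clusters of 20. Rounding up gives 54 clusters and 1,080 residents, as stated. Without the correction the total is 988, which does not match.

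**Step 2: effective sample size.** Completers per arm = 540 × 0.80 = 432. Two design effects are reasonable:
- the stated VIF: 432 / 2.425 = 178.1;
- 16 completers per cluster: 1 + 15 × 0.075 = 2.125, and 432 / 2.125 = 203.3.

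**Step 3: chance of a non-significant result.** With p₁ = 0.45, p₂ = 0.45 − d, p̄ their mean and nₑ the effective size,

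power = Φ[(d − 1.96·s₀) / s₁], s₀ = √(2p̄(1 − p̄)/nₑ), s₁ = √((p₁(1 − p₁) + p₂(1 − p₂))/nₑ).

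For d = 0.08:
- nₑ = 178.1: (0.08 − 1.96 × 0.0521)/0.0519 = −0.43, power 33.5%, non-significant 66.5%;
- nₑ = 203.3: (0.08 − 1.96 × 0.0488)/0.0486 = −0.32, power 37.4%, non-significant 62.6%.

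| True reduction in fallers | Non-significant, VIF 2.425 | Non-significant, design effect 2.125 |
|---|---|---|
| 5 points | 84% | 83% |
| 7.5 points | 70% | 67% |
| 8 points | 67% | 63% |
| 10 points | 51% | 46% |
| 15 points (planned) | 16% | 12% |

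An 8-point increase in fallers (45% to 53%) would be non-significant in about 67% and 64% of trials respectively.

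**Step 4: what a null result leaves open.** With 45% fallers in both arms, the 95% half-width is 1.96·√(2 × 0.45 × 0.55/nₑ): 10.3 points for nₑ = 178.1 and 9.7 points for nₑ = 203.3.

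An observed 45% against 37.5% would also be non-significant. With nₑ = 178.1 the standard error is √((0.45 × 0.55 + 0.375 × 0.625)/178.1) = 0.0520, and the interval for the reduction runs from −2.7 to +17.7 points. On the significance reading, this result would lead to a costs-only analysis while its interval still includes the 15 points the trial was designed to find.

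**The case against.** Much can fairly be said for the plan.

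- **The article does not say significant.** It says a difference must be observed, and the p ≤ 0.05 sentence is not linked to the economic section. The significance reading is an inference. This stands, but it does not rescue the rule: p ≤ 0.05 is the only criterion supplied, and the literal reading makes the second branch nearly void.
- **The plan does not claim proven equality.** A reader might infer that it treats a null result as proof of equal effectiveness. No sentence says so. Setting effects aside in the economic comparison only implies it.
- **The effect does not vanish.** The risk difference and its interval are reported unconditionally, and medical and nursing costs after falls are counted in both arms, so a real change in falls still moves the cost difference. This stands. What is lost is the joint summary of cost and effect, and the planned sensitivity analysis on key variables does not restore it.
- **The background does not make a biased conclusion likely.** A reader might argue that, because no tool has beaten clinical judgement, the rule will bias the result in the expected scenario. That does not follow. Those comparisons concerned predictive accuracy, and the article says effects on clinical endpoints have not been studied. If the true effect is near zero, a cost comparison does least harm. The article contains no cost figures, so neither the direction nor the size of any bias can be stated.
- **A condensed article leaves methods to a fuller plan.** This is fair for the choice of bootstrap or graphical display. It does not cover the switching rule, which is stated outright.

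**Conclusion.** The concern holds, with limited scope. The rule makes the form of the economic analysis depend on the primary result through an undefined trigger. On its only workable reading it sets effects aside when the trial cannot show them to be equal. A true 8-point reduction would fall into the costs-only branch in about 63 to 67% of trials, and a null result would leave differences of roughly 10 points in either direction unexcluded.

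These figures rest on 1:1 allocation, 20% loss spread evenly over clusters, the stated ICC and control risk, and a normal approximation. They change little between the two design effects.

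The primary endpoint, its analysis, the sample size and data collection are unaffected. Because only the secondary economic evaluation is touched, this should be fixed but does not undermine the trial.

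**What to change.** Delete the conditional rule. State that incremental mean cost and incremental proportion of fallers will be estimated together whatever the primary p-value, with uncertainty that respects clustering. A bootstrap that resamples whole clusters is one suitable method, and it keeps the correlation between cost and effect. Report the cost difference as one component of that result.

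If a costs-only form is to be kept, it would have to be limited to a confidence interval lying wholly inside an equivalence margin fixed in advance. With a half-width of about 10 points, that margin would need to exceed about 10 points even if the observed difference were zero, so this is the weaker option.

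The cost is a change of wording and a little more analysis. No new data are needed, since falls and resource use are already recorded. The change should be made before results are known, because a later choice would look driven by them.

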### Time plan

The pilot phase of the study started in September 2005. Consecutive recruitment of clusters has started at the same time and is expected to last 4 to 6 months.
